# DepActive: study protocol for a randomised controlled multicentre trial of telephone-delivered behavioural activation for the treatment of depression in older adults in primary care

**DOI:** 10.1186/s13063-024-08521-y

**Published:** 2024-10-05

**Keywords:** Behavioural activation, Depression, Depressive symptoms, Geriatrics, Older adults, Primary care

## Abstract

**Background:**

Depression is common in older adults and is related to reduced quality of life and functional ability as well as increased mortality and morbidity. Current guidelines recommend psychological treatments for the treatment of depression in adults. Studies show that about 30% of older adults with depression in Sweden receive pharmacological treatment and about 3% receive psychological treatment. However, a majority receive no treatment at all. There is a need for effective and scalable psychological treatment options for older adults with depression in primary care. Behavioural activation is an extensively evaluated, effective, and relatively simple treatment for depression that can be delivered by health care professionals without comprehensive training in psychological treatment.

**Methods:**

We will conduct a randomised controlled 2-armed parallel group multicentre trial comparing treatment as usual in primary care to a five-session telephone-delivered behavioural activation treatment as add on to treatment as usual. The current trial is open labelled. In all, 250 older adults (≥ 65 years) with depression will be recruited from primary healthcare centres in three Swedish regions. The primary outcome is depressive symptoms measured with the Montgomery Åsberg Depression Rating Scale – Self rating version (MADRS-S) after treatment and at 3- and 6-month follow-up. Secondary outcomes include depression diagnoses, activity level (self-rated and measured with accelerometer), and self-rated anxiety, daily functioning, quality of life, self-efficacy, and loneliness.

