### Primary outcome

The primary outcome is depressive symptoms measured with the Montgomery-Åsberg Depression Rating Self-rating Scale, MADRS-S [48]. The MADRS-S is a nine-item questionnaire designed to measure depression severity during the past 3 days.

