## Sample size

A total of 250 participants will be included in the trial. Sample size calculation is based on a previous meta-analysis of Behavioural Activation in older adults with mean effect sizes of 0.72 at post-treatment and 0.44 at follow-ups at 3–6 months [21], which is in line with our pilot study of telephone-based BA for older adults yielding an effect size of 0.85 at post-treatment [38] and 0.41 at 6 months post-treatment [44]. An effect size of 0.4 was chosen, based on previously mentioned meta-analysis and pilot study but also following recommendations on the lower value for an effect size corresponding to a medium-sized effect in gerontological research [62]. According to G*Power, 250 participants are needed in total to achieve 80% power with a significance level of 0.05 and a drop-out rate of 20% for analysis of co-variance, ANCOVA. The flow of this study will follow the Modified CONSORT Statement extension for individual randomised controlled trials of non-pharmacological treatments (Fig. 2) [63].

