## Statistical methods

The difference between the intervention group and control group in depressive symptoms post-intervention measured with MADRS-S will be estimated using analysis of covariance (ANCOVA) with baseline values on the MADRS-S as covariate as well as with the between-group effect size post-intervention using Cohen’s *d*. Difference from baseline between the groups post-intervention and long-term follow-ups (3 and 6 months) will be analysed separately with repeated measures ANOVA. All continuous secondary outcome measures will be estimated using ANCOVA and repeated measures ANOVA, whereas discrete outcomes (i.e. depression diagnosis) will be estimated using logistic regression. Attrition will be analysed using *T*-test for continuous measures (age, depression severity on the MADRS-S, cognitive functioning on the MMSE and FAB-Swe) and chi-square for sex. Analyses will be conducted both using intention-to-treat (ITT) as a primary analysis and per-protocol as a secondary analysis. In the ITT, all randomised participants will be included, whereas only participants that adhered to the treatment or control-condition will be included in the per-protocol analyses. Missing data will be handled by using multiple imputation. Stopping guidelines for trial termination due to negative effects is not applicable and no interim analyses are planned.

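### MADRS-S is the primary outcome at three time points and under two models, none named as deciding, while N = 250, alpha 0.05 and 80% power fit one ANCOVA comparison

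*Protocol article*

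**What the plan says.** Four places in the protocol article bear on this.

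- **Abstract, Methods.** The primary outcome is the "Self rating version (MADRS-S) after treatment and at 3- and 6-month follow-up". All three time points have equal standing.
- **Primary outcome.** "The primary outcome is depressive symptoms measured with the Montgomery-Åsberg Depression Rating Self-rating Scale, MADRS-S". The section gives no time point.
- **Statistical methods.** The post-intervention group difference in MADRS-S is estimated by ANCOVA with baseline MADRS-S as covariate. The next sentence adds: "Difference from baseline between the groups post-intervention and long-term follow-ups (3 and 6 months) will be analysed separately with repeated measures ANOVA". Intention-to-treat is the primary analysis and per-protocol the secondary one. The section ranks neither the time points nor the two models.
- **Sample size.** "An effect size of 0.4 was chosen". The total of 250, for 80% power, was calculated "with a significance level of 0.05 and a drop-out rate of 20% for analysis of co-variance, ANCOVA". This is the only significance level in the document. The effect size is justified by both post-treatment effects (0.72 and 0.85) and later ones (0.44 at 3 to 6 months, 0.41 at 6 months).

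**The concern.** A trial that claims a 5% false-positive rate needs one deciding test, or a rule that joins several. Here the published definition gives three primary time points, and one of them is analysed by two models. ANCOVA and a repeated measures ANOVA on change from baseline do not always agree on significance.

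Without a named deciding test, the time point or model could be chosen after the results are known. The trial is open label and its primary outcome is self-rated, so a reader would have good reason to ask whether the choice came first. The stated pair of 5% error and 80% power is guaranteed only for one named comparison.

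**Working it through.** **1. Reproduce the plan's own figure.** Inputs from Sample size: d = 0.4, alpha 0.05, power 80%, drop-out 20%. The 1:1 allocation is from Participants, recruitment, and randomisation. A two-sided test is assumed, because sidedness is not stated.

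- Normal approximation: n per arm = 2(1.960 + 0.842)² / 0.4² = 98.1, so 99 per arm and 198 in total; 198 / 0.8 = 247.5, so 248.
- Exact t distribution: 100 per arm; 200 / 0.8 = 250.
- ANCOVA F test with f = 0.2, two groups and one covariate: 199 in total; 199 / 0.8 = 248.75, so 249. Power with 200 completers is 80.4%.
- One-sided test: 156 / 0.8 = 195, which does not match.

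So 250 is right for one two-sided comparison at 0.05.

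**2. Count the intention-to-treat tests on MADRS-S.** The repeated measures sentence can be read in three ways:

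| Reading | Tests |
|---|---|
| ANCOVA at post-treatment, plus one repeated measures ANOVA over all visits, separate from the ANCOVA | 2 |
| ANCOVA at post-treatment, repeated measures at post-treatment, one repeated measures analysis of the long-term follow-ups | 3 |
| ANCOVA at post-treatment, repeated measures at post-treatment, at 3 months and at 6 months | 4 |

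Per-protocol runs are left out because the protocol labels them secondary.

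**3. Chance of at least one false positive.** For independent tests the formula is 1 − (1 − 0.05)^k: 14.3% for k = 3 and 18.5% for k = 4. These tests share data, so the true figures are lower and need simulation. Assumptions, none given in the protocol: no treatment effect, normal data, 100 completers per arm, correlation 0.3 to 0.5 with baseline and 0.5 to 0.7 between follow-ups. Each test is run at 0.05 and any one counts. Repeated measures ANOVA is tested by its group-by-time F test. There were 40,000 null trials for each of nine correlation pairs.

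| Tests | Middle case (0.4; 0.6) | Range over the grid |
|---|---|---|
| ANCOVA at post-treatment alone | 4.9% | 4.9 to 5.1% |
| Both post-treatment models, no follow-up | 7.3% | 7.1 to 7.7% |
| Two-test reading | 8.6% | 8.4 to 9.3% |
| Three-test reading | 11.0% | 10.6 to 11.3% |
| Four-test reading | 13.6% | 12.3 to 14.6% |

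Across the readings that include follow-up, the figure is about 9 to 14%. The two post-treatment models alone take it to 7 to 8%.

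**4. The opposite rule.** If success required all three time points to be significant, error would not be inflated. Power would then fall to about 57 to 61%. This was simulated as three ANCOVAs at the design effect, with an assumed common correlation of 0.3 to 0.8. Neither an any-of rule nor an all-of rule returns the stated pair of 5% and 80%.

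**The case against.** The strongest reply is that the intended primary test can be recognised. The post-treatment ANCOVA comes first in Statistical methods, it is the method named in Sample size, and intention-to-treat is called primary. On this view only a label is missing. An alpha rule is also commonly left to a statistical analysis plan, which is not shown.

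Much of this stands. The ANCOVA is probably what was meant, and the absence of a multiplicity rule is not held against the protocol. But the abstract gives the follow-ups the same primary status, and the effect size is justified by follow-up effects as well as post-treatment ones. A later plan could therefore settle the matter only by narrowing the published definition.

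Some stronger readings are tempting, and the document does not support them:

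- *At least four tests.* Four is the fullest of the three intention-to-treat readings above, not the minimum.
- *Each test at 0.05, any one sufficient.* The level appears only in Sample size, and no success rule is written. Both are conditions of the calculation, not statements of the plan.
- *An error rate more than double the nominal one, as a fact.* It fails on the two-test reading and is only just met on the three-test reading.
- *A loss of power from 80% to 66%.* The arithmetic is right for a t-test with 100 per arm at 0.05/3, but nobody plans that split. The design effect of 0.4 lies below both meta-analytic effects (0.72 and 0.44), so at those effects each single comparison at 0.05 has at least 80% power.

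**Conclusion.** The point holds as a failure to name the deciding time point and model. The primary outcome covers three time points, the post-treatment contrast has two models, and the sample size calculation fits one ANCOVA. The size of about 9 to 14% against 5% is conditional on unadjusted testing at 0.05, on any one result counting, and on the assumed correlations. It shows what the open wording permits, not what the sponsor has said it will do. The sample size itself is correct for a single comparison and needs no revision once that comparison is named.

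**What to change.** State in the protocol and the registration that the single primary analysis is the intention-to-treat ANCOVA of MADRS-S at post-treatment, adjusted for baseline MADRS-S, at a two-sided level of 0.05. Bring the abstract and the Primary outcome section into line with it. Make MADRS-S at 3 and 6 months secondary. Testing them in fixed order after the post-treatment result is one option, but it is not required. Label the repeated measures ANOVA of the post-treatment contrast as supportive; it need not be removed. Make the change before outcome data are compared by arm.

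The cost is one paragraph plus the ethics application and registry modification that Trial status already foresees for important changes. Recruitment is planned to run to June 2027. No extra participants are needed, and N = 250 with 80% power stands. The real price is that a benefit seen only at 3 or 6 months could not be reported as a primary success.

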**Discussion:**

There is a need for fully powered studies of brief behavioural activation for older adults with depression delivered by telephone in a primary care context. This study has the potential to improve first-line treatment of depression in older adults in primary care, consequently reducing morbidity and mortality within this population. Increasing the availability and accessibility to effective psychological treatment for depression in older adults is needed to meet future demographic changes.

**Trial registration:**

ClinicalTrials.gov: NCT06284889. Registered February 28, 2024.

**Supplementary Information:**

The online version contains supplementary material available at 10.1186/s13063-024-08521-y.

## Background

Depression is considered one of the leading causes of the global health burden across the entire lifespan [1]. The global prevalence of clinically relevant depressive symptoms in older adults is about 30% [2], and it is about 13% for major depressive disorder [3]. A study conducted in Swedish primary care showed a depression prevalence of 15% among adults aged 60 years or older [4]. Depression in older adults is associated with reduced quality of life [5] and reduced physical, cognitive, and social functioning and increases the risk for morbidity and mortality [6]. Depressive symptoms in older adults have also been shown to be able predict rehabilitation outcomes [7]. A recent United Nations prognosis indicate a continuously growing proportion of older adults with about 25% of the population in Europe and Northern America aged 65 years or over by 2050 [8]. The high prevalence of depressive symptoms in older adults and the upcoming demographical changes stress the need for effective and scalable interventions for the treatment of depression in older adults.

However, depression is a treatable condition and there are several treatment options for depression in older adults, including antidepressant medication, psychological treatment, and physical activity [9]. In the guidelines from the Swedish National Board of Health and Welfare regarding the treatment of depression in adults [10], antidepressant medication and psychological treatments, including cognitive behavioural therapy, are recommended first-hand, and physical activity is included as an alternative.

In Sweden, approximately 25% of older adults with depressive symptoms receive antidepressant medication, about 3% receive psychological treatment and a majority receive no treatment at all [11, 12]. Psychological treatments are effective for the treatment of depression in adults in general, with better long-term effects than pharmacological treatment [13]. Internationally, studies of various forms of physical activity for older adults have yielded mixed results on mental health outcomes [14–16]. An umbrella review has concluded that physical activity is effective in reducing depressive symptoms in older adults [17]. In a meta-analysis examining the effects of psychological treatments in different age groups, no significant differences were found between adults in general and adults aged 65 years or older [18]. Another meta-analysis has shown that cognitive behavioural therapy for depression is as efficacious for older adults as for young and middle-aged adults [19]. Also, most older adults with depression prefer non-pharmacological treatment to pharmacological treatment for depression [20].

One established psychological treatment for depression is behavioural activation (BA), a brief and structured intervention focusing on increasing engagement in adaptive activities and decreasing engagement in activities that maintain or increase the risk for depression [21]. Central interventions in BA are activity monitoring, which aims to give insight into how activities affect mood, and activity scheduling, which aims to increase the performance of meaningful and enjoyable activities through structured scheduling [22].

Behavioural activation is an extensively evaluated, effective, and relatively simple treatment for depression that can be delivered by health care professionals without extensive training in psychological treatment [23]. Several meta-analyses [23–25] have shown that BA is more effective than control conditions in treating depression. Fewer studies have examined the effect of BA in older adults and many of the existing studies are small [23]. However, a meta-analysis investigating the effect of BA for the treatment of depression in older adults indicate that BA is an effective treatment in this population [21].

One way to facilitate access to healthcare for older adults is to utilize telemedicine [26], that is, providing remote health care through electronic means of communication [27]. A recent meta-analysis investigating telemedicine interventions for depression and anxiety in older adults showed that interventions delivered by internet or telephone are feasible and efficacious [28]. Behavioural activation is feasible and effective for the treatment of depression delivered in a variety of formats including via internet [29], videoconferencing [30–32], and telephone [33–35]. However, it is important to note that studies investigating BA via telephone are small and several lack control group. Few studies have investigated telephone-based BA for older adults. One study by Marti and colleagues found that telephone-based BA reduced depressive symptoms and disability [36]. In a recent study by Gilbody and colleagues, telephone-based BA was found to have positive effects on depressive symptoms and emotional loneliness in older adults with long term conditions during the COVID-19 pandemic [37]. Our research-group conducted a pilot trial of brief telephone-based BA for older adults with depressive symptoms during the COVID-19 pandemic. The results suggest that the treatment is feasible, acceptable, and potentially efficacious [38].

There is a need for fully powered studies of brief behavioural activation for older adults with depression delivered by telephone in a primary care context during non-pandemic conditions as well as studies of behavioural activation in older adults in a Swedish primary care context. Drawing on the promising results from our pilot trial, we will now conduct a study to investigate the telephone-delivered BA treatment for older adults with depression in primary care.

## Objectives and hypothesis

The aim of the current study is to evaluate the effects of a brief telephone-based BA treatment for the treatment of depression in individuals 65 years and older in primary care.

We hypothesise that participants randomised to the treatment condition receiving the BA treatment will show a stronger decrease in depressive symptoms (primary outcome) and improve more on secondary outcomes, compared to participants randomised to the control group receiving treatment as usual (TAU).

## Methods

### Study setting and design

This study is designed as an open label randomised controlled 2-armed parallel group multicentre trial. The study will be conducted in primary care in the Swedish regions of Västmanland, Sörmland, and Uppsala. Initially, four primary healthcare centres (PHCs) will be included in the study, two in Västmanland, one in Sörmland, and one in Uppsala. All PHCs in these three regions received an invitation to participate in the study via the primary healthcare board in each region. Individual PHCs were selected based on logistical factors and their interest in participating. Additional PHCs, within these three regions, may be included if the recruitment of participants is insufficient from the initial four PHCs. A representative from The Swedish Partnership for Mental Health (NSPH) has been involved in the design of the study to improve feasibility for the participants. This RCT protocol is reported according to the recommendations specified in Standard Protocol Items: Recommendations for Interventional Trials (SPIRIT) [39], and the completed checklist is attached in supplementary material 1.

### Participants, recruitment, and randomisation

General practitioners (GPs) at each PHC will be responsible for identifying potential participants and provide interested patients with oral and written information about the trial. Eligible participants should be 65 years or older, present with depressive symptoms, understand Swedish well enough to understand the treatment materials, have access to telephone, and be interested in participating in the trial. Before enrolment, a more thorough clinical assessment is conducted by a study psychologist or study physician and the participants will be given oral information about the study and have opportunity to ask questions before signing an informed consent form. To be enrolled, participants should fulfil criteria for current minor or major depressive disorder according to the Diagnostic and Statistical Manual of Mental Disorders 5th edition, DSM-5 [40]. The exclusion criteria are (1) current psychological treatment, (2) severe depression, (3) elevated suicide risk, (4) severely impaired vision or hearing, (5) current substance use disorder, (6) current or previous manic or hypomanic episodes, (7) current or previous psychotic disorder, and (8) current diagnosis of minor or major neurocognitive disorder or suspected neurocognitive disorder (Mini Mental State Examination result < 25). Concomitant anti-depressant medication is permitted if no changes were made regarding dose or type of anti-depressant medication within the past 8 weeks.

All participants that provide informed consent and fulfil the inclusion criteria and not any exclusion criteria will consecutively be randomised to either the control group receiving TAU or the treatment group receiving TAU with the addition of the BA treatment. The randomisation will be conducted by a study psychologist or study physician after the baseline assessment is completed. Study randomisation will be conducted using Study Randomizer [41], a web-based randomisation service. Participants will be randomly allocated to either control or intervention group (1:1) via random sized blocks of two, four, or six. The researcher conducting the follow-up diagnostic interviews will be blinded to participant allocation, GPs at the PHCs will not be blinded to patient allocation.

## Interventions

### Treatment group

The treatment group will receive TAU with the addition of a five-session telephone-based BA-intervention over an 8-week period. The telephone-based BA-intervention is based on a treatment protocol called Behavioural Activation for Primary Care, BA-PC [42, 43], that was translated and adapted to Swedish by our research group and subsequently used in a pilot study of BA in isolated older adults with depression during the COVID-19 pandemic [38, 44]. Fourteen of the participants were interviewed on their experiences of the treatment [45], and one suggestion from several of the participants was to add one follow-up call, a so-called booster session. Another suggestion that has been implemented in this version of the treatment is to conduct the first treatment session in-person.

In the planned study, the treatment will consist of five treatment sessions, with sessions 1 through 4 conducted once a week and session 5 conducted 4 weeks after session 4. Session 1 will be conducted in-person, and the following sessions will be conducted by telephone. The estimated session length is 45–60 min for session 1 and 30–45 min for sessions 2 through 5. The session outline is described in Table 1. There will be no special criteria for discontinuing or modifying allocated interventions.

**Table 1 Tab1:** Session outline for the BA treatment

Session no	Session components
1	Present the treatment materials Assess mood and suicide risk Provide psychoeducation about depression Provide treatment rationale for behavioural activation (BA) Provide rationale and instructions for activity log If highly motivated for change, plan activity for coming week
2	Follow-up on mood and suicide risk Review activity log Discuss life goals and values Plan activities aligned with life goals and values for coming week
3	Follow-up on mood and suicide risk Review activity log Troubleshoot any problems carrying out activities Plan activities aligned with life goals and values for coming week
4	Follow-up on mood and suicide risk Review activity log Troubleshoot any problems carrying out activities Plan activities aligned with life goals and values for coming week Instruct the participant to independently plan activities aligned with life goals and values until the booster session
5	Follow-up on mood and suicide risk Review activity log Troubleshoot any problems planning or carrying out activities Review treatment Create a maintenance plan

All study therapists will receive a 1-day training on the BA protocol, provided by a licenced clinical psychologist who also was responsible for the translation of the study manual. The training will include a review of the treatment protocol and the treatment materials, roleplay of critical procedures in the treatment, and discussions about common challenges in BA treatment and ways to handle these challenges. Throughout the study period, all study therapists will attend biweekly online supervision sessions led by the same psychologist that provided the BA training. To further promote adherence to the BA protocol, a checklist of key session components will be filled out by the study therapist at the end of each session.

